### Sample size calculation

2.4

The sample size was computed assuming a repeated measures ANOVA with a within-between interaction using g*Power 3.1 (Faul et al., 2009) with the sleep duration used as primary outcome measure. We assumed a middle effect size (*d* = 0.25), a power of 0.90 and an alpha-error of 5%. This resulted in a minimum sample size of *N* = 46 participants. As we expect a drop-out rate of about 25%, the target enrollment is 60 participants.

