### Data analysis

2.9

The study is conducted using a control design in which the control group receives regular group therapy. To detect treatment effects, variance in between intervention and control group at T0 and T1 (see Figure 1) is assessed by using a repeated measures ANOVA including two factors (GROUP and TIMEPOINT). Significance level is set to be at *p* = 0.05. Post-hoc tests will clarify effect size and direction. If statistical assumptions are not met, non-parametric alternatives will be used. In additional exploratory analyses we plan to account for sociodemographic aspects or the influence of different diagnoses for the efficacy of the program.

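### Section 2.4 labels the planning effect d = 0.25, but N = 46 matches f = 0.25, a 1.0-SD difference in change; at d = 0.25 and correlation 0.5, power is about 38% or 13%, not 90%

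*Protocol article*

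**What the plan says.** Section 2.4 (Sample size calculation) describes the method as follows: "The sample size was computed assuming a repeated measures ANOVA with a within-between interaction using g*Power 3.1", "with the sleep duration used as primary outcome measure". The inputs are given in one sentence: "We assumed a middle effect size (*d* = 0.25), a power of 0.90 and an alpha-error of 5" per cent. The result is "This resulted in a minimum sample size of *N* = 46 participants", raised to 60 enrolled to allow for drop-out.

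Section 2.9 (Data analysis) fixes the design that this calculation has to match: "variance in between intervention and control group at T0 and T1 (see Figure 1) is assessed by using a repeated measures ANOVA including two factors", namely group and timepoint, so two groups and two measurements. It also says "Significance level is set to be at *p* = 0.05".

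The article gives no correlation between the two measurements, no standard deviation, no target effect in minutes of sleep, and no conversion from d to another effect measure.

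**The concern.** d and f are different scales. The G*Power procedure named in 2.4 takes f as its effect size, and the article prints d. If the printed symbol is taken at its word, a reader concludes that 46 participants give 90% power for a quarter-SD effect. If 0.25 went in as f, the calculation assumed something four times as large on the scale of the difference in change.

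The distinction affects how the result will be read. T0 and T1 are one week apart, and section 3.1 (Limitations) itself asks whether two sessions are enough to establish new habits. A trial able to detect only a 1.0-SD difference over that interval could well be non-significant when a worthwhile smaller effect exists. A reader relying on 2.4 would have no warning of this.

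**Working it through.** **Inputs.** From 2.4: effect size 0.25, power 0.90, alpha 5%, total N = 46. From 2.9: k = 2 groups, m = 2 timepoints. Assumed: equal groups (the article describes alternating blocks but gives no ratio) and correlation rho = 0.5, the G*Power preset, varied below.

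**Formula.** For the within-between interaction, power comes from a noncentral F with lambda = f² × N × m / (1 − rho), df1 = (k − 1)(m − 1) = 1 and df2 = (N − k)(m − 1) = N − 2.

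**Step 1: reproduce the plan's figure.** With f = 0.25, rho = 0.5 and N = 46, lambda = 0.0625 × 46 × 2 / 0.5 = 11.5 and power is 0.912. At N = 44 power is 0.8997, just under target, so the smallest even N is 46: an exact match. Variants that do not match are three timepoints with f = 0.25 (36), a one-sided test (36), and lambda defined as f²N or f²(N − k) (172 or 174).

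**Step 2: what f = 0.25 means here.** The variance of a T0-T1 change is 2σ²(1 − rho). A t-test comparing mean change between two arms of N/2 therefore has squared noncentrality D²N / [8σ²(1 − rho)], where D is the between-group difference in change. Setting this equal to 2f²N / (1 − rho) gives D = 4fσ. With f = 0.25, D = 1.0 SD of the outcome. At rho = 0.5 the SD of change equals the outcome SD, so it is also 1.0 SD of change. Check: a two-sample t-test with 23 per arm and a 1.0-SD difference also gives power 0.912.

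**Step 3: power if d = 0.25 is literal.** There are two readings.

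- Reading A: d converted as f = d/2 = 0.125, so D = 0.5 SD. At rho = 0.5, lambda = 0.015625 × 184 = 2.875.
- Reading B: d is the difference in change itself, D = 0.25 SD, so f = 0.0625. At rho = 0.5, lambda = 0.00390625 × 184 = 0.719.

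| Correlation | Power at N = 46, reading A | Power at N = 46, reading B | N for 90%, A | N for 90%, B |
|---|---|---|---|---|
| 0 | 22% | 9% | 340 | 1348 |
| 0.3 | 29% | 11% | 238 | 944 |
| 0.5 | 38% | 13% | 172 | 676 |
| 0.7 | 57% | 19% | 104 | 406 |
| 0.8 | 75% | 26% | 70 | 272 |

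If all 60 enrolled were analysed, power at rho = 0.5 would be 48% (A) and 16% (B).

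**Step 4: correlation needed to rescue the printed figures.** Power of 90% at N = 46 requires rho of about 0.87 under reading A and about 0.97 under reading B.

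**Step 5: in minutes, as illustration only.** The article gives no SD for sleep duration. If it were 45 to 75 minutes (assumption), 1.0 SD would be 45 to 75 minutes of extra sleep relative to control, and 0.25 SD would be about 11 to 19 minutes (0.25 × 45 and 0.25 × 75).

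**The case against.** The strongest reply is that 0.25 was meant as f all along. The named procedure works in f, 0.25 is called a middle effect, and N matches f = 0.25 exactly. On that reading 90% is arithmetically right and the error is one wrong letter. Much of this stands, and it is the more likely account. It does not clear the paragraph: the printed effect is still wrong, and nothing tells the reader that the assumed effect is a 1.0-SD difference in change.

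Three stronger readings are tempting, and the article does not support them.

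- A reader might infer that N = 46 can arise only from f = 0.25. It cannot be put so firmly, because the correlation is not printed. With f = 0.125 and rho = 0.875, lambda is 0.015625 × 92 / 0.125 = 11.5, the same as in step 1, so N is again 46. Nothing in the article points to such an input, but it is not excluded.
- A reader might infer that the trial simply has 13% to 38% power and needs 172 or 676 patients. Those figures hold only at rho = 0.5 and only if d = 0.25 is the true design effect.
- A reader might count the drop-out allowance as a further error, since 60 × 0.75 = 45, one short of 46. The article says about 25%, and 45 completers still give 90.6% power under f = 0.25. This carries no weight.

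Nor is the unprinted correlation a fault by itself, since a condensed article may leave it to the full protocol. It matters here because the printed effect, power and N cannot be reconciled without it.

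**Conclusion.** Section 2.4 is wrong as written. The match in step 1 makes it very likely that 0.25 was entered as f and printed as d, so the 90% applies to a 1.0-SD between-group difference in T0-T1 change. That identification rests on the preset correlation of 0.5 and equal groups. The equivalence of f = 0.25 and 1.0 outcome SD does not depend on the correlation.

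The conclusion that 46 participants do not give 90% power for d = 0.25 holds under either reading of d for every correlation examined from 0 to 0.8. It would fail only at the undocumented values in step 4. The defect is a mislabelled effect measure that conceals a large assumed effect. It is not shown that the authors' own calculation was under-powered for the effect they entered.

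**What to change.** Ask the authors to check the saved G*Power inputs and then restate 2.4 from them. The paragraph should:

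- replace d = 0.25 with the effect measure actually entered (apparently f = 0.25), and drop or qualify the description of it as middle-sized;
- state the correlation between T0 and T1 that was used;
- give the implied between-group difference in change, which is 1.0 SD of the outcome if f = 0.25 is confirmed, and preferably also in minutes of sleep with the SD assumed;
- report the power of 46 participants for smaller differences: about 38% for 0.5 SD and about 13% for 0.25 SD if the correlation was 0.5, recalculated otherwise;
- note that a non-significant result would not exclude a small or medium effect.

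The cost is one reworded paragraph and a less favourable statement of power. If f = 0.25 is confirmed, no extra patients and no change to the analysis are needed. If the authors instead confirm that d = 0.25 was the intended design effect, they must also give the correlation that led to 46 and justify it.

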### Randomization

2.5

Intervention and control group run in alternating turns. Patients are assigned to the condition and undergo the study procedure as scheduled for the condition as soon as enough patients were admitted to the day patient department. After one group completes the intervention, a break of 8–10 weeks follows, after which the other group begins (i.e., after an intervention group and the described break a control group follows) Therefor participants are quasi-randomized into their assigned condition. This process is repeated until the estimated sample size is met.

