### Study design

2.1

The study is conducted using a waitlist-control-design. Each participant attends three sessions in a group therapy setting, with session T0 and T1 forming the primary focus to detect a treatment effect (Figure 1). The third timepoint, T2, serves for further exploratory analysis and to deliver the intervention to the control group as well. Two out of three sessions are the RfL-sessions, while a third one is of an unrelated topic. Participants are quasi-randomized into intervention or control group. Allocation of participants to the group is based on the time they begin treatment in the facility. Whether the participants belong to the control or intervention group is determined by the alternating nature of their occurrence. After an intervention group lasting 28 days an about 8–10 weeks pause interval follows to reach a sufficient amount of new, naive-to-the treatment admissions. After that a control group of 28 days starts, also followed by an 8–10 weeks pause interval afterwards. This process, alternating between intervention and control group with an 8–10 weeks pause interval in between, is continued until the required number of participants has been reached. Participation from start to end lasts 28 days representing 4 weeks around the described timepoints. The measurements collected for this study consist of different self-report questionnaires, sleep logs and actigraphy data. Psychometric properties of the questionnaires used are described below.

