In this study actigraphy will only be used in terms of assessing treatment effects on sleep duration (Total Sleep Time, TST). Therefor the MotionWatch 8 (Alpha Trace Ltd.) a wrist worn actigraphy watch worn continuously throughout the 28 day will be used. We will use MotionWatch Mode 1 and record 30 s epochs of movement and light information. Further analysis of actigraphy data such as sleep efficiency and the stability of sleep–wake-rhythm and all efforts to compare subjective and objective sleep data will be described in the additional protocol mentioned above.

At the end of the intervention participants provide feedback about perceived usefulness of the metaphor and materials, adherence during the intervention, intention to further adhere to the introduced behavior and further annotations, positive and negative. We further collect sociodemographic variables such as age, gender, living situation and completed and intended education, as well as current psychiatric disorders (ICD-10 diagnoses) and mental health problems. With this we intend to gain insight into the usefulness of the intervention across various psychiatric disorders and their respective symptom severity on an exploratory level.

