### Study sample and setting

2.2

The study is conducted as a multicenter-study in three day clinics for children and adolescent psychiatry in northern Germany. Participating clinics comprise of the day clinic facility of the Clinic for Child and Adolescent Psychiatry, Psychotherapy and Psychosomatics at the Center for Integrative Psychiatry, School of Medicine in Kiel and the two day clinics of the Department for Child and Adolescent Psychiatry and Neurology at the Rostock University Medical Center in Rostock. All patients and parents/custodians receive age-appropriate information about the study procedure and the collection of data. The collection of study data is only possible if written informed consent is granted by both, children and parents/custodians. Depending on the facility, groups consist of different age ranges overall ranging from 10 to 18 years. Age-related differences regarding time needed to fill out questionnaires and worksheets are accounted for by personnel to ensure the programs practicability across all age groups. Groups may vary in size depending current treatment capacity. Inclusion criteria for this study are rather limited: To take part in the study the patients need to be between 10 and 18 years old, being treated in the facility consistently for the whole duration of the study and need to be able to comprehend presented concepts such as time. Further a sufficient understanding of the German language as well as the ability to read and write short phrases is required. Patients that do not consent to their data being processed take part in the intervention nevertheless. They fill out the questionnaires and sleep logs relevant to the intervention, but those will not be collected for analysis and no actigraphy will be recorded.

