Also, in children and adolescents, subjective sleep quality is not only a result of overall mental wellbeing, but there is a clear bidirectional association. Poor self-perceived sleep quality has been shown to increase the risk of anxiety, depression and stress symptoms later on (Zou et al., 2020). Especially in the context of changing sleep characteristics during adolescence, both sleep duration and quality seem to be crucial factors predicting later strain from mental health problems (Thompson et al., 2024; Tarokh et al., 2014). When taking a look at psychiatric samples it is even more evident that sleep problems occur comorbidly with many different psychiatric disorders such as ADHD, autism or depression (van der Heijden et al., 2018; Gupta et al., 2019). Sleep problems may even serve as a common thread linking various psychiatric disorders (Boafo et al., 2021). Diminished sleep quality can also interfere with treatment success of psychotherapy as well as symptom severity at discharge (Buysse et al., 1999; Boafo et al., 2021). Conversely, a reduction of sleep problems helps to improve the outcome of disorder-specific psychotherapy (Freeman et al., 2020). Summarizing the current evidence on the role of sleep in mental wellbeing, and considering the limited resources and options for mental health professionals for addressing sleep problems (Freeman et al., 2020), this underlines recurrent calls for transdiagnostic interventions targeting sleep (Vestergaard et al., 2024; Boafo et al., 2021; Tarokh et al., 2014). This may either be as a form of treatment or as prevention (Boafo et al., 2021). If proven to be efficacious, “Ready for Landing” aims to offer an option to answer those needs by providing a transdiagnostic, economic and easily implementable sleep hygiene intervention. It also seeks to provide knowledge about sleep and sleep hygiene to mental health professionals to sensitize for this matter as advised by Freeman et al. (2020). By improving sleep hygiene, sleep quality, and sleep duration it could therefor positively influence the bidirectional relationship between sleep disturbances and psychiatric disorders and contribute to improved psychological wellbeing in children and adolescents. Some studies propose sleep hygiene interventions to be a first line treatment when targeting sleep problems in the psychiatric context (Baranwal et al., 2023; Chung et al., 2018; Peach et al., 2016), while other studies suggest stand-alone sleep hygiene interventions are lacking substantial treatment effects in the treatment of sleep disorders like insomnia (Irish et al., 2015; Chung et al., 2018). Those studies underscore that if still implemented, sleep hygiene interventions should be done in a standardized and comprehensive delivery of content, rather than relying solely on brochures or psychoeducation. “Ready for Landing” addresses this by following the manual we seek to evaluate here, by incorporating elements from CBT-I, and by helping patients understand the functionality and necessity of sufficient sleep while encouraging them to build routines enabling them to improve their sleep related behaviors (Lin et al., 2018). The combination of CBT-I and its inherent elements of sleep hygiene education has further been proven to be efficacious (Hertenstein et al., 2022). Further by addressing both subjective sleep quality and objectively measured sleep duration the study aims to investigate the effect the intervention has on the parameters known to be influential on mental wellbeing (Vestergaard et al., 2024; Zou et al., 2020). It systematically evaluates the effects as demanded many times when talked about currently available sleep hygiene interventions (Nikles et al., 2020; McLay et al., 2024). If the effects are as proposed, “Ready for Landing” can be seen as an effective, theory-driven intervention to specifically target important domains of generic sleep problems.

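### Time in day-clinic treatment at T0 is not limited in the protocol and not in the primary model, although the arms come from different admission periods: a small possible bias with a cheap remedy

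*Protocol article*

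**What the plan says.** The Study design section makes the arm depend on calendar time: "Allocation of participants to the group is based on the time they begin treatment in the facility". Intervention and control turns alternate. After each turn, "an about 8–10 weeks pause interval follows to reach a sufficient amount of new, naive-to-the treatment admissions". The Randomization section adds that patients enter the condition then due "as soon as enough patients were admitted to the day patient department"; it does not define how many are enough. On the length of a turn: "Participation from start to end lasts 28 days representing 4 weeks around the described timepoints".

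The only requirement on time in treatment looks forward. Under Study sample and setting, a patient must be "being treated in the facility consistently for the whole duration of the study". No limit is set on time already spent in treatment at T0, and no typical length of stay is given.

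On data, the Questionnaires and actigraphy section says: "We further collect sociodemographic variables such as age, gender, living situation and completed and intended education", followed by ICD-10 diagnoses and mental health problems. Admission date and time in treatment are not named, but the list is introduced as examples. The Data analysis section fixes the treatment comparison as a repeated measures ANOVA at T0 and T1 with two factors, GROUP and TIMEPOINT. Adjustment for sociodemographic aspects or diagnoses is exploratory. The Limitations section names season, light, temperature and holidays as possible confounders and argues that the short delay limits them.

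**The concern.** All participants receive day-clinic psychiatric treatment alongside the study, so the change from T0 to T1 includes whatever that treatment does to sleep in the same week. The Discussion gives a reason to expect some effect: in children and adolescents, "subjective sleep quality is not only a result of overall mental wellbeing, but there is a clear bidirectional association". If sleep changes faster at one stage of a stay than at another, and one arm's turns happen to catch more patients at that stage, part of the ordinary course is counted for or against the intervention.

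Randomisation would balance treatment stage in expectation. Here the balance rests on admission flow in separate calendar periods, over what may be few turns, and the stated model has no term that could correct an imbalance. Adjusting for the T0 score alone would not be enough either, since two patients with the same score can be on different slopes.

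**Working it through.** **1. The plan's own sample size.** Inputs from Sample size calculation: effect 0.25 (labelled d), power 0.90, alpha 5%, repeated measures ANOVA with within-between interaction. Not stated and therefore assumed: correlation ρ = 0.5 between the two measurements, sphericity correction 1, m = 2 timepoints.

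- λ = f² · N · m / (1 − ρ), with 1 and N − 2 degrees of freedom.
- f = 0.25, N = 46: λ = 0.0625 × 46 × 2 / 0.5 = 11.5, power 0.912. N = 44 gives 0.8997. So N = 46 reproduces with f = 0.25.
- Read literally as d = 0.25 (f = 0.125), the same calculation gives N = 172. The planning effect is therefore f = 0.25.

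**2. What f = 0.25 means as a difference in change.** With two equal arms, λ = δ² · N / 4, where δ is the between-arm difference in T0–T1 change in units of the SD of change. So δ = √(11.5 × 4 / 46) = 1.0. At ρ = 0.5 the SD of change equals the outcome SD, so the planned difference is 1.0 outcome SD. This is the benchmark for any bias.

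**3. Possible spread of time in treatment at T0.** Inputs from Study design.

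- Admitted during the pause: 0 to 56–70 days.
- Admitted early in the preceding 28-day turn but not part of it: up to 28 + 56 = 84 to 28 + 70 = 98 days.

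These are upper bounds. The length of stay, which is not stated, may cap them.

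**4. Size of a possible bias.** The documents give no figure, so both inputs are assumptions: the share of recently admitted patients differs by 40 percentage points between arms, and recently admitted patients change by 0.1–0.3 SD more than others over the one week from T0 to T1.

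- Bias = 0.40 × 0.1 = 0.04 SD, to 0.40 × 0.3 = 0.12 SD.
- Relative to the planned difference of 1.0 SD: 4% to 12%.

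**5. Effect on the error rate.** With no treatment effect and a shift b in the difference in change, the two-sided 5% t-test on change has noncentrality b / √(4/N) and N − 2 degrees of freedom.

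| Shift b (SD) | Error, N = 46 | Error, N = 60 |
|---|---|---|
| 0.04 | 5.2% | 5.3% |
| 0.12 | 6.8% | 7.4% |
| 0.2 | 10% | 12% |
| 0.3 | 17% | 21% |

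The first two rows are the range from step 4. The last two show how the error grows under larger assumed shifts. To reach them through a 40-point imbalance, the weekly change would have to differ by 0.5 SD (0.2 / 0.40) or 0.75 SD (0.3 / 0.40).

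**6. Price of adjustment at N = 46.** One covariate costs one degree of freedom in the test of change. If it shares R² with arm and residual variance does not fall, λ becomes 11.5 × (1 − R²). Power is 0.912 at R² = 0, 0.898 at 0.05, 0.882 at 0.10 and 0.843 at 0.20. The R² values are assumptions.

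**The case against.** The strongest reply is that nothing in the design favours one arm. The same start rule and the same pause precede both kinds of turn, the order is fixed by alternation, and the contrast spans one week. The GROUP × TIMEPOINT test removes differences in level at T0. The article calls the allocation quasi-randomised and discloses confounding from the waitlist design. It is also a condensed report, and fuller variable lists may stand elsewhere.

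Much of this stands. A reader might make four stronger inferences that the documents do not support:

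- That time in treatment is not collected. The list of variables is open, and allocation itself uses the start of treatment, so the clinics must know the date.
- That patients at T0 do range from days to months in treatment. This is a ceiling derived from the pause, and the length of stay is not given.
- That unblinded staff steer the mix between arms. The arm order is fixed and the stated pause varies by only about two weeks.
- That the protocol itself says sleep changes at different rates early and late in a stay. The Discussion states an association in both directions between sleep and wellbeing; dependence on treatment stage is an added assumption.

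What the reply does not remove is that equal rules do not make non-concurrent arms exchangeable. One turn plus pause lasts 12–14 weeks (4 + 8 to 4 + 10), so an intervention–control cycle lasts 24–28 weeks, about half a year. Each arm's turns may then recur near similar points of the calendar. If admissions follow holidays or seasons, an imbalance in treatment stage need not average out. The primary model is also stated outright, with two factors and no covariate, so its form is not merely left open.

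**Conclusion.** The point holds as a minor one. Time in treatment at T0 is unrestricted by the protocol, its mix may differ between non-concurrent arms, and the stated primary model does not account for it. Bias follows only if sleep changes at a rate that depends on treatment stage, which is plausible but not quantified anywhere in the documents. Its direction is unknown.

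A reader might set the assumed 0.04–0.12 SD against the stated d = 0.25 and call it 16–48% of the effect. That benchmark is wrong, because N = 46 reproduces only with f = 0.25. Against the implied 1.0 SD difference in change the figure is about 4–12%, with a two-sided error of about 5–7% instead of 5%. These results rest on the assumed 40-point imbalance, the assumed weekly difference of 0.1–0.3 SD and ρ = 0.5.

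**What to change.** Take days since admission at T0 from the clinic record for every participant. Tabulate it by arm and by turn. Pre-specify it as a covariate, with its TIMEPOINT interaction, in the primary T0–T1 model; the interaction is the part that matters, because it lets the rate of change depend on treatment stage. Name treatment stage in the Limitations section beside season and holidays.

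The cost is one date that the clinics already hold and one degree of freedom. Power at N = 46 stays at about 0.912 if the covariate is unrelated to arm and falls to about 0.88 at an assumed R² of 0.10. A larger loss would itself show that arm and treatment stage are entangled, which readers need to know. The covariate reduces one source of confounding. It does not repair the non-concurrent allocation, and the report should not present it as doing so.
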